**Methods and analysis:**

The study will constitute secondary analyses of UK data (from the British Household Panel Survey and the Understanding Society study). Merging these datasets gives coverage of the period from 1994 to 2016. Missing data will be handled using multiple imputation. The primary outcomes are the rates and inequalities in initiation, experimentation, escalation to daily smoking and quitting among youths aged 11–15 years. Secondary outcomes include the prevalence of smoking among parents of these youths. Discrete-time event history analysis will be conducted to examine whether changes in the probability of youth smoking transitions are associated with the implementation of the smoke-free public places legislation; and whether any observed effects differ by socioeconomic position and parental smoking. A multilevel logistic regression model will be used to investigate whether there is a step change or change in trend for the prevalence of parental smoking after the policy was implemented. The models will be adjusted for relevant factors (including cigarette taxation, the change in the legal age for purchase of cigarettes and e-cigarette prevalence) that may be associated with the implementation of the legislation.

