**Figure 2 F2:**
[figure not shown]
Smoking stages for early adolescents. Adapted from ‘Socioeconomic position and early adolescent smoking development: evidence from the British Youth Panel Survey (1994–2008)’ by Green *et al*.^47^

Using population representative longitudinal survey data, we will address the following research questions:Q1. Has the implementation of the smoke-free public places legislation in the UK been associated with a step change or change in the trend in the probability of youth smoking transitions?Q2. Has the implementation of the smoke-free public places legislation in the UK been associated with a step change or change in the trend in the inequalities in the probability of youth smoking transitions?Q3. (A) Has the implementation of the smoke-free public places legislation in the UK been associated with a step change or change in the trend in the prevalence of smoking among parents of UK youths? (B) Does the observed change (if any) differ by socioeconomic position?Q4. (A) Do changes in parental smoking explain any impact of the smoke-free public places legislation on the probability of youth smoking transitions? (B) Has the implementation of the smoke-free public places legislation in the UK been associated with any change in the strength of the association between parental smoking and the probability of youth transitions? (C) Does the observed change (if any) differ by socioeconomic position?Q5. How distinct are the impacts of the smoke-free public places legislation from the impacts of the change in the legal age for purchasing tobacco, the increasing prevalence of e-cigarettes and the changes in tobacco taxation on youth smoking transition?

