### Statistical analysis

Discrete-time event history analysis^53^ will be conducted to examine whether changes in the probability of youth smoking transitions are associated with the implementation of the smoke-free public places legislation (Q1). The implementation of smoke-free legislation is viewed as a natural experiment,^41 54^ and analyses will examine if there is a step change or change in trend in the probability of smoking transitions after the country-specific implementation dates for the smoke-free legislation (ie, 2006 for Scotland, 2007 for the rest of the UK). Youth will only be considered at risk for a transition once they have made the previous transition (ie, they are only at risk for experimentation once they have tried smoking). Thus, data for each analysis will be right censored at the year of the smoking transition (or age 15 years) and left censored prior to the previous transition (or age 11 years). Escalation to daily smoking and quitting will be treated as two alternative outcomes, which young people will be at risk of once they commence occasional smoking. In line with previous work,^47^ youths who skipped smoking transition stages will be treated as making the intervening transitions in the same year. For instance, youths who transited from never having tried smoking to ex-smoker in the same year will be treated as having progressed to occasional smoker and having quit within the same year (but not as having escalated to daily smoking). Analyses will be adjusted for age, gender, the overall temporal trend in rates (which may encompass effects of other temporal increases in tobacco control) and overall differences in rates between UK countries.

We will then examine whether any effects observed on youth smoking transition differ by socioeconomic position (Q2). Parental education level will be used as an indicator of socioeconomic position. In cases where parental educational qualification for both parents differs, the higher qualification will be used. This will be added to the predictive models, alongside interactions with the variables representing the implementation of the legislation.

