A multilevel logistic regression model (with person-years nested within persons) will be used to investigate whether there is a step change or change in trend for the prevalence of parental smoking (any current smoking by either parent) after smoke-free public places legislations were implemented in the UK (Q3A) and whether observed changes (if any) differ by socioeconomic position (Q3B). This model will include all years of data for all respondents without any right or left censoring and will be adjusted for the young person’s age, gender, the overall temporal trend in parental smoking and overall differences between UK countries. The second stage of the modelling will additionally include parental education and interactions between parental education and the variables representing the implementation of the legislation.

Next, building on the models developed to assess whether the impact of the legislation on youth smoking transitions varied by socioeconomic position (Q2), parental smoking will also be included and we will assess whether this explains any observed differences associated with the implementation of the legislation (Q4A). We will test for interactions between parental smoking and the variables representing the implementation of the legislation to see if the influence of parental smoking changes after the legislation (Q4B) and then for a three-way interaction between parental smoking, legislation implementation and socioeconomic position to see if this varies by socioeconomic position (Q4C).

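### The scale on which inequality is judged (Q2, Q3B) is not fixed: the product terms described answer on a ratio scale questions posed as probabilities and prevalence

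*Protocol article*

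**What the plan says.** The Abstract makes inequality a primary matter: "The primary outcomes are the rates and inequalities in initiation, experimentation, escalation to daily smoking and quitting". Under Aims/objectives/research questions, Q2 asks about a step change or "change in the trend in the inequalities in the probability of youth smoking transitions". Q3 is worded as the prevalence of parental smoking, and the aims promise to find how much of any impact runs through parents.

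The Statistical analysis section then gives the methods:

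- **Q1 and Q2.** "Discrete-time event history analysis^53^ will be conducted to examine whether changes in the probability of youth smoking transitions are associated with the implementation". No link function is named. For Q2, parental education is the indicator of socioeconomic position: "This will be added to the predictive models, alongside interactions with the variables representing the implementation of the legislation".
- **Q3A and Q3B.** "A multilevel logistic regression model (with person-years nested within persons) will be used to investigate whether there is a step change or change in trend". The second stage adds parental education and "interactions between parental education and the variables representing the implementation of the legislation".
- **Q4A.** Building on the Q2 models, "parental smoking will also be included and we will assess whether this explains any observed differences associated with the implementation of the legislation (Q4A". No decomposition and no scale is named.

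The Introduction describes tobacco control tightening step by step over the period, and the models adjust for an overall time trend. The Discussion gives wider inequality in youth uptake as its example of a negative impact of the ban.

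**The concern.** A product term in a logistic model tests whether the odds ratio between education groups changed. In a complementary log-log (cloglog) model it tests whether the hazard ratio changed. Neither tests whether the gap in probability changed. When the overall level is moving, as the article expects, the two can point in opposite directions. Nothing in the article says which one defines widening or narrowing.

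What is at stake is the direction of the headline statement. A policy under which the disadvantaged group gained more percentage points could be reported as having widened inequality. With the scale left open, it could also be chosen after the results are seen.

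Q4A raises a related, smaller matter. In a non-linear model, adding a strong predictor rescales the other coefficients. A before-and-after comparison of the legislation coefficient therefore mixes mediation with rescaling.

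**Working it through.** The article gives no rates, effect sizes or sample size, so there is no figure of its own to reproduce. **Every rate below is an assumption**, used to show what can happen and how large it is.

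**1. Inequality in youth transitions (Q2).** Assume low- vs high-education annual risks of 12% vs 6% before and 7% vs 3% after.

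- Absolute gap: 12 − 6 = 6 points before; 7 − 3 = 4 points after. It narrows.
- Odds ratio before: (0.12/0.88)/(0.06/0.94) = 2.14. After: (0.07/0.93)/(0.03/0.97) = 2.43. Interaction OR = 2.43/2.14 = 1.14, which reads as widening.
- Under a cloglog link the hazard ratio is ln(1 − p₁)/ln(1 − p₂). Before: ln(0.88)/ln(0.94) = 2.07. After: ln(0.93)/ln(0.97) = 2.38. Same direction, so the unstated link does not remove the problem.
- Equal legislation OR of 0.7 in both groups: 0.7 × 0.1364 = 0.0955 in odds, or 8.71%; 0.7 × 0.0638 = 0.0447 in odds, or 4.28%. The interaction is null, yet the gap goes from 6.0 to 4.4 points.
- The scales need not disagree. With 12% vs 6% falling to 8% vs 4%, the gap narrows from 6 to 4 points and the OR also falls slightly, from 2.14 to 2.09.

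**2. Inequality in parental smoking (Q3B, logistic stated).** Assume 50% vs 25% falling to 40% vs 17%. The gap goes from 25 to 23 points. The OR goes from 1.000/0.333 = 3.00 to 0.667/0.205 = 3.25, an interaction OR of about 1.09.

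**3. Mediation (Q4A), logit link assumed.** Let m be the share of youths with a smoking parent, d the direct log-OR of the legislation and b = ln 2.5 the parental effect:

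P(m, d) = (1 − m)·expit(a + d) + m·expit(a + b + d)

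Take d = −0.20 and m falling from 0.40 to 0.37.

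*Common transition, a = −0.6* (risk 35% with non-smoking parents, 58% with a smoking parent, 44% overall):

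- P(0.40, 0) = 0.44397; P(0.40, d) = 0.39763; P(0.37, d) = 0.39106.
- Total effect in log-odds: logit(0.39106) − logit(0.44397) = −0.2178.
- Share by coefficient change: (0.2178 − 0.20)/0.2178 = 8.2%.
- Share on the probability scale: (0.39763 − 0.39106)/(0.44397 − 0.39106) = 0.00657/0.05291 = 12.4%.
- No mediation (m stays at 0.40): total −0.1903, so coefficient change gives (0.1903 − 0.20)/0.1903 = −5.1% where the truth is 0.

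*Uncommon transition, a = −2.5* (8% with non-smoking parents, 11% overall): total −0.2245. Coefficient change gives 0.0245/0.2245 = 10.9%; the probability scale gives 0.00242/0.02072 = 11.7%.

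*No direct effect (d = 0):* both methods give 100%, so the discrepancy needs a direct effect.

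*Cloglog with the same inputs:* 5.7% vs 12.6% for the common case; 11.5% by both methods for the uncommon one.

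**4. Range.** A second set of scenarios used a logit link, a direct OR of 0.8 and parental smoking falling from 40% to 35% or 30%. Measured against an indirect effect on one common log-odds scale, coefficient change missed about 1–10% of that effect when the risk with non-smoking parents was 3–6% and the parental OR 2–3. It missed about 7–40% when that risk was 20–40% and the parental OR 2–5.

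**The case against.** The strongest reply is that this is silence in a condensed article. Product terms in logistic or hazard models are the usual test of effect modification, and a relative measure of inequality is legitimate. Nothing rules out predicted probabilities or a formal decomposition, and a fuller analysis plan may contain both. The rates above are invented, and they show that the scales can disagree, not that they will.

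Much of this stands. A reader might infer that inequality and mediation will be judged only on log-odds. The article does not say so. Logistic regression is named for Q3 alone, a logit link for Q2 and Q4A would be an inference, and how Q4A will assess explanation is left open. A reader might also infer that part of the mediated effect is always hidden. The working does not support that either: the effect disappears without a direct effect and is negligible for uncommon transitions.

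What the reply does not meet is the inequality point. The article does choose its inequality tests. Those tests do not by themselves answer questions worded as probability and prevalence, and the direction of the answer carries a policy conclusion.

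**Conclusion.** The point holds for Q2 and Q3B. The article poses inequality in probabilities and prevalence, describes only ratio-scale tests, and attaches a negative verdict to widening without saying on which scale. Under plausible but assumed falls in level, the direction can reverse: a gap of 6 narrowing to 4 points alongside an OR rising from 2.14 to 2.43, with the same direction under cloglog. This is a gap in specification worth closing before analysis. It is not an error in the models.

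The Q4A point is secondary and conditional. It applies only if mediation is judged by coefficient change. It matters when there is also a direct effect in the same direction, the transition is common and parental smoking is a strong predictor (8.2% vs 12.4% in the assumed case). Experimentation, escalation and quitting are modelled only among youths already past an earlier stage, so higher annual probabilities are plausible there, but the article gives none.

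**What to change.** Keep the planned models and add post-estimation.

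- **Q2 and Q3B.** Compute standardised probabilities by parental education with the legislation terms switched on and off, at stated post-legislation years because both a step and a trend are modelled. For Q3B, average over the person random effect. Report the change in both the absolute difference and the ratio, with delta-method or bootstrap intervals, and state widening or narrowing separately for each scale.
- **Q4A.** Report direct and indirect effects on the probability scale, or KHB-corrected coefficients if a logit link is used, with bootstrap intervals clustered by household. Name the link for the transition models.

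The cost is a little extra post-estimation work and the need to report two inequality measures that may disagree. No new data are needed. The change does not address confounding between parental and youth smoking, which the Introduction already acknowledges as the stronger assumption.

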Although its primary purpose was to prevent harm to the public, especially non-smokers, from SHS, the smoke-free public places legislation in the UK was also expected to improve air quality in public places and reduce health risks associated with smoking among smokers.^15^ Importantly, the legislation was also expected to contribute to changes in social attitudes and norms towards smoking by reducing the acceptability of smoking, especially in social places like pubs and restaurants and other public spaces shared with non-smokers.^16 17^ For example, research on implementation of smoke-free legislation in Massachusetts, USA, showed that smoking became less socially acceptable, and social norms shifted to favour smoke-free environments.^18^ Impacts on adult behaviour and societal norms are critical to understanding how and why a ban might impact on youth smoking, as youths are unlikely to smoke in the public places affected by the legislation. Any effect on youth smoking could be through changes in adult smoking behaviour, and the implications this has for social norms and the availability of cigarettes to young people given that adults are a major source of cigarettes for youth smokers.^19 20^ Thus, effects of legislation may not be immediate but may grow over the years following the implementation of the legislation as these effects accumulate.

Parental smoking is a key influence on children’s smoking uptake,^5 21^ and thus may be a major mechanism by which smoke-free legislation impacts on youth smoking. There are at least two potential mechanisms: impacts on the prevalence of parental smoking and displacement of smoking behaviour (see figure 1). First, regarding the prevalence of parental smoking, while studies tend not to show long-term effects of legislation on overall smoking prevalence, heterogeneity of impact among subgroups of smokers is still largely unexplored.^8 22^ Smokers who live with their children are one subgroup among whom smoking legislation and its associated social changes might be expected to have a stronger impact. Social denormalisation of smoking via smoke-free legislation may raise adults’ consciousness and awareness of potential harms, especially around children and non-smokers.^23^ Concerns about the health of children may then provoke cessation attempts. If parental smoking reduces after a ban, then decreases in youth uptake might be expected to follow.

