Randomised controlled trials, often seen as the gold standard for establishing causality, are ethically and practically problematic in the context of studying population-level policies such as the smoke-free legislation. However, implementation of smoke-free public places legislation in the UK, which occurred in 2006 in Scotland and 2007 in the rest of the UK, provides the opportunity for a natural experimental approach^41^ to studying the impact of this policy on youth uptake, and the mechanisms by which these impacts occur. A natural experimental approach requires weaker assumptions for observed effects to be interpreted as causal than in most observational epidemiological studies. Specifically, if we were to observe that both parental smoking and the implementation of smoke-free legislation were associated with youth smoking uptake (thinking of parental smoking generally rather than in the context of this policy change), then causal interpretations of these associations both require an assumption of no (unmeasured) confounding. However, this assumption is considerably stronger for parental smoking (ie, that no other factor is causing both parental smoking and youth smoking) than for the timing of the legislation (ie, that no other factor causing/coinciding with the implementation of the legislation implementation also causes changes in youth smoking uptake).

Nevertheless, even for the implementation of smoke-free legislation, the assumption of no confounding may be problematic as the policy has not been the only important change happening in the UK that might impact on youth smoking uptake. Though acknowledged as one of the most significant changes in policy, smoke-free legislation was implemented in the UK within a period of incrementally increasing tobacco control.^42^ For example, sales taxes applied to cigarettes are subject to ongoing change, and the implementation of smoke-free legislation also coincided closely with a 2007 change in the legal age for purchase of cigarettes from 16 to 18 years. Another factor is the availability and use of e-cigarettes which has been growing in the UK since 2011.^43^ To attribute changes in youth smoking to the smoke-free policies, we will need to differentiate the impacts of the policy from these other contextual changes.

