### Data

Data from the British Household Panel Survey (BHPS) Youth Sub-Sample and Understanding Society, both of which are freely available to bona fide researchers from the UK Data Archive under their normal terms and conditions,^48 49^ will be used in this study. Both Understanding Society and BHPS studies obtained consent for data sharing from their participants. More information on the data sources, consent and sampling can be found on BHPS and Understanding Society websites https://www.iser.essex.ac.uk/bhps and https://www.understandingsociety.ac.uk/, respectively. Data on youths’ (11–15 year olds) and parents’ smoking history, and parents’ socioeconomic position from the BHPS (covering the period 1994–2009) will be merged with those of the recent Understanding Society Survey (from 2009 to 2016). The merger of these datasets gives coverage of the period from 1994 to 2016, with data from 2016 newly released in November 2017. As such, 9–10 years of postlegislation data will be available in the dataset. This amount of postlegislation data will be important in investigating the immediate as well as the long-term impact of the smoke-free public places legislation on youths smoking transition. Respondents will be included for each year they were aged 11–15 within this period (ie, a maximum of 5 years of data per respondent).

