A final step will be to adjust the above models for relevant factors that may be associated with the implementation of the legislation. This will include annual levels of cigarette taxation, the change in the legal age of purchase for cigarettes from 16 to 18 in 2007 for England, Wales and Scotland, and in 2008 for Northern Ireland (ie, the implementation date differs from that of the smoke-free legislation by 1 year in Scotland and Northern Ireland), and survey estimates of the annual prevalence of e-cigarettes from 2012^55^ (with e-cigarette prevalence coded as 0 prior to that date). As an additional sensitivity test, we will rerun analyses with the date of ban implementation transposed either 5 years forward or backward in time. If observed effects are genuinely attached to the ban rather than overall temporal trends, these transposed ‘placebo’ effect estimates should be weaker or null compared with those observed at the actual ban implementation dates.

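### The placebo-date test leaves the real 2006/2007 break unmodelled in the data, so a genuine ban effect can produce non-null and sometimes larger placebo estimates

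*Protocol article*

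**What the plan says.** The main models (Protocol article, Statistical analysis) look for a "step change or change in trend in the probability of smoking transitions after the country-specific implementation dates", with those dates given as "2006 for Scotland, 2007 for the rest of the UK". They adjust for age, gender, country and an overall temporal trend.

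The last paragraph of that section adds a sensitivity test: "we will rerun analyses with the date of ban implementation transposed either 5 years forward or backward in time". Its reading rule is that, if the effects truly belong to the ban, the placebo "effect estimates should be weaker or null compared with those observed at the actual ban implementation dates". No data window is given for these reruns, no term for the real ban is said to stay in the model, and the rule does not say whether the step or the trend change is judged.

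Three other statements bear on the test:
- Data: "The merger of these datasets gives coverage of the period from 1994 to 2016", and "9–10 years of postlegislation data will be available in the dataset".
- Introduction, on the expected shape of the effect: "effects of legislation may not be immediate but may grow over the years following the implementation of the legislation".
- Introduction, on other influences: "the availability and use of e-cigarettes which has been growing in the UK since 2011". The adjusted models carry e-cigarette prevalence as a covariate from 2012, set to 0 before then.

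**The concern.** Read plainly, moving the date replaces the real break with a false one and refits the same years. If the ban had an effect, that effect is still in the data, but no term in the placebo model describes it. The false step and trend-change terms then pick up part of it.

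The test is meant to separate a ban effect from a general time trend, in a design whose causal claim rests on timing. A contaminated placebo makes it misleading in one direction: a real effect can look as if it were not tied to the ban date. The difficulty is greatest for a delayed, growing effect, which is the shape the Introduction anticipates.

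**Working it through.** **Inputs from the article.** Years 1994–2016; real dates 2006 (Scotland) and 2007 (rest of the UK); shifts of −5 (2001/2002) and +5 (2011/2012) years; step and trend-change terms. Side check: 2016 − 2007 = 9 and 2016 − 2006 = 10, which agrees with the stated follow-up. The article gives no figure for the placebo test to reproduce.

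**Assumptions.** Linear background trend of −0.03 per year; Scotland 9% of the sample; yearly sample size from 2009 multiplied by 1 or 2.5; baseline log-odds in 2005 of −1.5 to −2.5, which moves the trends below by about 0.001 and the steps by about 0.01. All effects are on the log-odds scale.

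**Model.** For shift s, with T = 2006 or 2007 by country and P = 1 from year T + s onward:

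logit(p) = a + c·Scotland + b·year + δ·P + γ·P·(year − T − s)

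Expected probabilities were generated with a known effect at s = 0, and the model was refitted at s = −5, 0 and +5 on all years.

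**Results (multiplier 1).**

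| True effect | Term | −5 | Real date | +5 |
|---|---|---|---|---|
| Step −0.30 | step | 0.002 | −0.300 | −0.050 |
| | trend change | −0.028 | 0 | 0.018 |
| Trend change −0.05/yr | step | 0.08 | 0 | −0.16 |
| | trend change | −0.033 | −0.050 | −0.043 |
| Step −0.30 and trend −0.05/yr | step | 0.085 | −0.300 | −0.22 |
| | trend change | −0.062 | −0.050 | −0.026 |
| Starts 3 years late, −0.06/yr | trend change | −0.022 | −0.042 | −0.059 |
| Accelerating, −0.006 × years² | trend change | −0.028 | −0.052 | −0.081 |

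**Reading, like term with like.**
- Pure step: the placebo steps are near null, so the rule is met.
- Pure trend change: 0.033/0.050 = 66% and 0.043/0.050 = 86%. These are weaker, but far from null.
- Step and trend together: 0.062/0.050 = 124% at −5. The rule fails on the trend term, although both placebo steps are weaker.
- Delayed effect: 0.059/0.042 = 140% at +5. The rule fails. With multiplier 2.5 it is −0.059 against −0.046.
- Accelerating effect: 0.081/0.052 = 156% at +5. The rule fails.

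If only a trend-change term is fitted, a least-squares version (Scotland 9–20%) puts the +5 placebo for a pure trend change at 116–145% of the real value and the −5 placebo at 89–101%.

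**With sampling noise** (300 simulated data sets, 600 at risk per year, Scotland 9%, multiplier 2.5; all assumed). A step of −0.4 with a trend change of −0.05/yr gives a −5 placebo trend larger than the real one in 88% of runs. A pure trend change of −0.08/yr gives a significant placebo trend in 73% (−5) and 38% (+5).

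**After the change.**
- Backward placebo on pre-ban years only, or with the real-date terms kept: exactly 0 for all five shapes, because the true effect is zero on every pre-ban row.
- Forward placebo on post-ban years only: 0 for the first three shapes, because their effect is linear in year after the ban and is absorbed by the intercept, country and trend terms. For the delayed effect it still gives a trend change of −0.048 and a step of −0.073, so the trend remains above the real-date −0.042 (with multiplier 2.5 the two are about equal, −0.046). For the accelerating effect it gives −0.060 against −0.052. Keeping the real-date terms gives the same values.

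**The case against.** A reader might infer that any genuine ban effect fails the plan's rule. The documents do not support that. The rule asks for weaker or null, not null, and a pure step or a pure trend change passes in expectation when both terms are fitted and like is compared with like. Setting a placebo trend against a real-date trend of 0, or a placebo step against a real-date step of 0, makes those cases look like failures only by switching coefficient. The Introduction gives no length of lag, and growth that starts at the ban in a straight line is the pure trend case.

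A reader might also infer that a real effect would be discarded. The article calls this an additional sensitivity test and attaches no such consequence. The main inference rests on the real-date terms, the policy adjustments and the parental-smoking pathway. A fuller plan could also state a data window.

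On e-cigarettes, the prevalence covariate comes before the placebo reruns in the same paragraph, so the reruns may include it. That is a partial answer: the covariate is 0 before 2012, while the Introduction dates the rise from 2011.

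What remains is that the article states both a procedure and a rule for reading it, and following them literally can mislead about timing. Step and trend effects together, or a delayed or accelerating effect, break the rule on the matching term.

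**Conclusion.** The point holds in a conditional form. As written, the placebo estimates are contaminated by the real break. They can exceed the real-date estimate: 124% for the −5 trend change in the combined example, and 140% and 156% for the +5 trend change in the delayed and accelerating examples. Where the rule is met for a trend change, a placebo at 66–86% of the real value says little.

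The exact sizes depend on the assumed effects, sample profile and linear background trend; the leakage itself does not. The conclusion takes the reruns to use all years with no real-date term, which is what the text implies but does not say outright. The forward date has a further weakness, since 2011/2012 coincides with the rise of e-cigarettes. The primary estimates are untouched. This is a should-fix.

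**What to change.** Amend the sensitivity paragraph before results are seen:
- Fit the backward placebo on pre-ban person-years only (to 2005 in Scotland, to 2006 elsewhere), or keep the real-date step and trend-change terms in every placebo model.
- Compare step with step and trend change with trend change, and say so.
- State that the forward placebo is uninformative about a delayed or growing effect, even after truncation, and that its date overlaps the e-cigarette rise. Say whether the prevalence covariate is in that model.

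The cost is a few sentences and a data filter, plus wider intervals. The backward placebo would have 5 years after the false date (2001–2005 or 2002–2006), with 7 or 8 years before it. A null result from so short a window should be read with its interval, not as proof of no effect.
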